### Economic analysis

The cost-consequences analysis will be undertaken from the perspective of the hospitals to determine if the sterile water injection is a cost-effective measure to reduce back pain in labour compared to the normal saline injection
[55]. Direct costs will be measured for mother and baby from consent to participate in the study until discharge from hospital and mothers and babies re-admission to the same hospital within 28 days of births. Information about resource use and costs will be collected at each site. The study will conduct a bottom-up costing for the intervention and pain-relief methods at each site. The costs included in the study are: costs for the intervention (1 ampoule of sterile water or normal saline (10 ml), 2 x 1 ml syringes, 2x1 25 gauge needles, 2 alcohol prep swabs and the midwives’ time to administer the intervention, costs of care in labour, birth, postnatal and neonatal admission, and re-admission costs within 28 days of births. Costs will be allocated to the relevant resource items using appropriate values. For example, staff time will be costed using hourly award rates plus on-costs; and the costs of care in labour, birth and postnatal in hospitals will be costed using appropriate Diagnosis Related Groups.

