### Gaps in the research on SWI as pain relief in labour

This will be the first clinical trial statistically powered to identify if the addition of SWI to standard maternity care is superior to standard care alone with CS rates as the primary outcome. Furthermore, there is limited information about analgesia, epidural anaesthesia use and birth outcomes following sterile water injections in labour. For example, it is not clear whether rates of instrumental vaginal deliveries are affected by the intervention. Combined results from the two trials
[40,41] measuring this outcome show a trend towards an increased instrumental birth rate in the SWI group (OR 1.91; 95% CI 0.95-3.84). Finally, none of the trials have included a cost benefit analysis; we intend to undertake such an analysis.

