#### Control

Participants in the control group will receive 0.1 – 0.3 millilitres of normal saline 0.9% for injection into the same four anatomical points surrounding the Michaelis rhomboid as previously described. Repeat injections will also be provided as required (Figure 
3).

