### Secondary outcomes

•Proportion of women undergoing induction and/or augmentation of labour

•Proportion of women receiving epidural anaesthesia

•Proportion of women having instrumental vaginal births

•Primary indication for CS

•Visual analogue scale of back pain prior to SWI

•Visual analogue scale of back pain following SWI (10, 45 minutes)

•Length of 1st stage and 2nd stage of labour

•Results of most recent vaginal assessment prior to randomisation

•Position of fetal occiput in relation to the maternal pelvis prior to randomisation and how this was determined

•Proportion of women breastfeeding at discharge

•Proportion of neonates admitted to the neonatal intensive care unit

•Cost of care from admission in labour until discharge of mother and baby from hospital from the perspective of the health system.

•Experience of satisfaction, relaxation, social support, negative side effects and memory of pain.

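### Costing the saline placebo procedure in the control arm removes most of the cost of giving SWI from the increment, and the cost window and perspective conflict between sections

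*Protocol article*

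**What the plan says.** The Economic analysis section sets its aim as "to determine if the sterile water injection is a cost-effective measure to reduce back pain in labour compared to the normal saline injection". Its cost list opens with "costs for the intervention (1 ampoule of sterile water or normal saline (10 ml), 2 x 1 ml syringes", continues with needles and swabs, and then takes in the midwives' "time to administer the intervention, costs of care in labour, birth, postnatal and neonatal admission". The list is given once for either product, and no sentence limits any item to the SWI arm.

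Under Control, the comparison group receives "millilitres of normal saline 0.9% for injection into the same four anatomical points surrounding the Michaelis rhomboid as previously described", with repeats available. Randomisation and blinding has two midwives other than the primary midwife give the injections in both arms, and cites a repeat-dose request rate of about 10% from the earlier trial. Care during labour defines standard care by its usual analgesic options, and saline injection is not among them.

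The cost outcome is described in three places:
- **Secondary aims:** labour, birth and the inpatient postnatal period, from the health system's perspective.
- **Secondary outcomes:** "Cost of care from admission in labour until discharge of mother and baby from hospital from the perspective of the health system".
- **Economic analysis:** the hospitals' perspective, with costs counted "from consent to participate in the study until discharge from hospital and mothers and babies re-admission to the same hospital within 28 days".

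**The concern.** A saline injection is the right control for a blinded comparison of caesarean section (CS) rates, but it is not something a hospital would buy. The decision that a hospital-perspective analysis should inform is SWI or usual care. If the placebo procedure is charged to the control arm, the materials and staff time for giving SWI are largely subtracted away, and SWI looks nearly free to administer.

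The second problem is that the start, end and perspective of the cost outcome all differ between sections. Recruitment and consent process places consent after admission, so the windows do not hold the same costs. Costs between admission and consent fall before randomisation; they should balance on average but add noise. Readmission costs fall after birth and could differ by arm if mode of birth does. With more than one definition in print, the one to report could be chosen after the data are seen.

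**Working it through.** The article states no procedure cost and no incremental cost, so there is no plan figure on this point to reproduce.

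**Step 1. Procedure part of the increment.** Let k be the cost of one injection procedure (materials and staff time), and rT and rC the proportions having a repeat on SWI and on saline.
- As planned: k(1 + rT) - k(1 + rC) = k(rT - rC).
- Against usual care, where no injection is given: k(1 + rT).
- Understatement: k(1 + rT) - k(rT - rC) = k(1 + rC).

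**Step 2. Repeat rates.** Applying the cited 10% to both arms (an assumption), the planned procedure increment is 0, the usual-care increment is 1.10k, and the understatement is 1.10k. If repeats were more common on saline, say 5% on SWI and 20% on saline (assumed for illustration), the planned increment is 0.05k - 0.20k = -0.15k. The usual-care increment is 1.05k and the understatement 1.20k. SWI would then appear cheaper to administer than giving nothing.

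**Step 3. A yardstick from the article.** The Background gives A$3,626-8,907 for vaginal birth and A$8,022-15,229 for CS. Pairing low with low and high with high (an assumption), the differences are 8,022 - 3,626 = A$4,396 and 15,229 - 8,907 = A$6,322. Sample size plans for 17.5% against 12.5%, a 5-point fall:
- 0.05 x 4,396 = A$219.8 per woman
- 0.05 x 6,322 = A$316.1 per woman

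**Step 4. Size under assumed staff costs.** Time and wages are not in the article. Assume 15-30 minutes per midwife at A$40-70 per hour, ignoring consumables.

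| Case | Cost per woman | Share of saving |
|---|---|---|
| Two midwives, first dose only | 2 x 0.25 x 40 = A$20 to 2 x 0.5 x 70 = A$70 | 20/316.1 = 6% to 70/219.8 = 32% |
| Two midwives, with 10% repeats | A$22 to A$77 | 22/316.1 = 7% to 77/219.8 = 35% |
| One midwife, first dose only | A$10 to A$35 | 10/316.1 = 3% to 35/219.8 = 16% |

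**Step 5. When it would matter most.** At 1.1k, the understatement equals the whole 5-point saving only if k is 219.8/1.1 = A$200 or 316.1/1.1 = A$287, well above the assumed A$20-70. At a 1-point fall in CS the saving is 0.01 x 4,396 = A$44 to 0.01 x 6,322 = A$63, and the top of the assumed range (A$70) exceeds it.

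**Step 6. The three cost definitions side by side.**

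| Section | Start | End | Perspective |
|---|---|---|---|
| Secondary aims | labour | inpatient postnatal period | health system |
| Secondary outcomes | admission in labour | discharge of mother and baby | health system |
| Economic analysis | consent | discharge, plus same-hospital readmission within 28 days | hospitals |

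**The case against.** The best reply is that the comparator is stated openly and costing both arms as delivered is consistent with it. The analysis is called cost-consequences, a format that normally shows components separately, so the SWI procedure cost may remain visible. The article gives no formula for the increment, and the full economic plan is not shown. Re-costing also makes a hybrid, pairing usual-care costs with outcomes from women who had saline injections. Charging SWI for two non-primary midwives would import staffing that exists partly for blinding.

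The points about the hybrid and the staffing stand and shape the fix. The others soften the concern without removing it: the cost list as written covers both products, and nothing takes the placebo procedure out of the control arm.

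Stronger readings are tempting but not supported:
- *The cost result favours SWI whatever the data show.* It does not. Total cost also depends on mode of birth, epidural use, length of stay, nursery admission and readmission. The Background itself reports a trend to more instrumental births with SWI (OR 1.91; 95% CI 0.95-3.84), which could make SWI the dearer arm.
- *The procedure increment is zero by construction.* It is k(rT - rC), and zero only when repeat rates are equal.
- *Analgesia is counted twice, bottom-up and again in Diagnosis Related Group prices.* The article does not say the two are summed, or what the group price contains.
- *The trial will analyse the wrong comparison*, because the Gaps in the research section says it will "identify if the addition of SWI to standard maternity care is superior to standard care alone with CS rates as the primary outcome". That is background wording about CS rates. Null hypothesis, Study design and Control all specify placebo or saline, so no analysis changes.

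**Conclusion.** The concern holds as a bias of known direction in one secondary outcome. As written, the procedure cost of SWI nets out apart from repeat doses, and the increment against usual care is understated by k(1 + rC), about 1.1k if the cited 10% repeat rate applies on saline. Under the assumed staff times and wages this is about 6-32% of the saving from the planned 5-point CS reduction before repeats, and less if one midwife would do the task routinely. That is enough to matter for a cost-effectiveness statement, but not enough by itself to decide it at the design effect.

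The percentages rest on assumed wages and times and on the end-to-end pairing of the Background costs. The upper cost figures vary with insurance status, and women with private insurance status are excluded, so A$316 may be too high a yardstick. The primary CS comparison is untouched.

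The conflict over window and perspective needs no assumption; it stands on the text.

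**What to change.** 1. In the base case, cost the placebo procedure at zero in the control arm. Charge SWI its procedure cost, including repeats, at the staffing expected in routine use.
2. Report the as-randomised costing, with the procedure charged in both arms, as a sensitivity analysis.
3. State as a limitation that re-costing cannot remove any effect of the saline injections themselves on outcomes.
4. Choose one start (admission or consent), one end (discharge, or with 28-day readmission) and one perspective (health system or hospital). Use them in Secondary aims, Secondary outcomes and Economic analysis.
5. As a minor consistency edit, reword the sentence in Gaps in the research to compare SWI plus standard care with placebo injection plus standard care.

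The cost is wording and one changed input, plus an estimate from the sites of routine staffing for the procedure. No new arm is needed. SWI will look slightly less favourable on cost in the base case.

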### Study duration

Study enrolment will commence after HREC approval is obtained at each site. Enrolment is expected to continue for 18–24 months across all sites; recruitment rates have been conservatively estimated based on our previous trial. The study duration will be three years and the primary endpoint will be time of birth.

## Trial governance

To assist with trial governance Collaborative Trial Agreements (CTA) will be established between each of the trial sites and the sponsor (ACU). Site investigators that are signatories to the agreements will be required to provide reports on site activities at the quarterly Research Team meetings and liaise with the Project Manager on an ongoing basis. Case report data on each participant will be collected directly from state and/or hospital databases, de-identified and stored on a password protected database. The case report data will be managed by the Project Leader, or designated research team member and made available to Principal Investigator.

## Staff training

### Administration of SWI

Sterile water injections are currently in use at some sites. Each of the sites in which SWI is already utilised have developed protocols, clinical guidelines for the use of SWI and training and competency documents based on information provided previously by the members of the research team. Therefore there is already a standard approach to SWI at these sites. A number of the sites do not currently use SWI and will be provided with training materials by the researchers, forms for assessing competency is contained within the trial documentation for use by these sites. The training will consist of workshops provided by the researchers and access to an online education resource. This resource will be available to all staff at each of the sites and can be accessed via any internet connected computer. This process will ensure a consistent approach to the administration of the interventions. The procedure is more commonly undertaken by midwives, however particularly in regional sites, other clinicians for whom the administration of injections is a normal part of their scope of practice, may also receive training in SWI administration.

### Study processes

The researchers will hold regular in-service sessions at each site to provide staff with information about the study processes and procedures, specifically, participant recruitment, consent and data collection. The in-service sessions together with support from the site co-ordinators will ensure trial integrity across sites. As consent will be undertaken during labour, to ensure similar information is provided to all women during the consent process, a guideline script will be provided to staff for use when discussing the trial.

## Ethical aspects

Human Research Ethics Committee (HREC) approval for all current sites has been provided by the Royal Brisbane and Women’s Hospital HREC, according to the single site HREC approval for multicentre clinical trials guidelines. Research governance approval has been provided by the Research Governance Office at each site.

### Potential risks

No adverse events, allergic or systemic reactions to the procedure have been reported in the literature other than the brief stinging sensation immediately following administration
[51].

### Data safety and monitoring

A multidisciplinary (statistician, clinical expert and research expert) Data and Safety Monitoring Committee (DSMC) will review all adverse events, which will also be reported by site staff to the participating institution’s Human Research Ethics Committee. In the case of complications or adverse events, participants will continue to receive routine care and have access to the research staff named in this protocol. The DSMC, which will be blinded to treatment allocation, will undertake interim analysis for safety and/or efficacy once 50% of the women have enrolled. The interim analysis will assess for any untoward outcomes and ensure sample size and power calculations are appropriate based on the observed difference between groups for the primary outcome.

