### Sample size

The meta-analysis of SWI use reported the overall rate of ‘in labour’ CS as 9.9% in the control group and 4.6% in the intervention (SWI) group
[36] – i.e. a greater than 50% reduction in the CS rate in the SWI group. However, the review included trials where women receiving SWI were compared with women receiving either a placebo or other interventions (eg. acupuncture), and included trials that were conducted over two decades ago (1990 to 2008): a significant increase in CS rates (% in 1991
[49] to 31.5% in 2009
[50]) has been recorded in the intervening period.

More recently, at a metropolitan hospital in QLD, routine birth outcome data were collected on all women in labour who received SWI during 2010 (n = 427). The CS rate for women in the SWI group was 12.5%. The ‘in labour’ CS rate for women receiving standard care during the same period was 17.5%. This represents a difference of 30% which we suggest may conservatively reflect the contemporary clinical trend in CS rates. To demonstrate a similar reduction (17.5% to 12.5%), our study requires 839 women in each group (80% power, type I error 0.05). The attrition rate in our previous trial was 13%
[48], however this was largely due to women giving birth prior to the measurement of the primary outcome (pain at 30 mins) and the use of nitrous oxide inhalation prior to randomisation. Neither of these are exclusion factors in this trial, therefore we expect attrition to be minimal and propose an attrition rate of 10%. The total sample size required is therefore 1886 women. As some sites have higher annual birth rates than other sites, the recruitment allocation anticipated for each site will be proportional.

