## Outcome measures

### Primary outcome

•Proportion of women who have a CS in labour

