## Data analysis

### Statistical methods

All women who underwent randomisation will be analysed in their allocated treatment groups (ie. intention to treat). Relative risks with 95% confidence intervals for the primary outcome will be calculated. Secondary outcome measures of categorical data will be analysed with chi-squared tests and continuous data will be analysed with t-tests for normally distributed data and Mann–Whitney *U* test for parametric data. Regression will be used if necessary to adjust for any other confounding variables. All study outcomes will be analysed using a two-sided P value of < 0.05 to indicate statistical significance. The study is only powered to report the primary outcome and for secondary outcomes confidence intervals (CI) will be included as a measure of the effect size. Differences in pre and post VAS scores will be reported in the format recommended by the recent Cochrane Review
[54].

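### The DSMC is blinded to allocation with no stated route to the arm identities, so at the one described interim look it can see the size of a difference but cannot say whether sterile water is the better or the worse arm

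*Protocol article*

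**What the plan says.** Under Data safety and monitoring, the protocol article sets up a three-discipline committee with two duties.

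- Ongoing: "Data and Safety Monitoring Committee (DSMC) will review all adverse events". Review by arm is not mentioned.
- At half enrolment: "The DSMC, which will be blinded to treatment allocation, will undertake interim analysis for safety and/or efficacy once 50% of the women have enrolled". The look is also to check for untoward outcomes and to "ensure sample size and power calculations are appropriate based on the observed difference between groups for the primary outcome".

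The primary outcome is "Proportion of women who have a CS in labour". The Sample size section supplies the planning rates: "To demonstrate a similar reduction (17.5% to 12.5%), our study requires 839 women in each group (80% power, type I error 0.05". Testing is two-sided (Statistical methods), and the alternative hypothesis is a relative difference of at least 30% with no direction attached.

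The section Gaps in the research on SWI as pain relief in labour reports that two earlier trials combined "show a trend towards an increased instrumental birth rate in the SWI group (OR 1.91; 95% CI 0.95-3.84").

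The Abstract describes the double blind as covering participants, clinicians and research staff. The committee's blinding is stated only under Data safety and monitoring.

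**The concern.** An interim review for safety or efficacy has to answer a directional question: is the experimental treatment doing good or doing harm? A committee that does not know which group received sterile water cannot answer it. More caesareans on SWI and more caesareans on saline lead to different advice. The first raises whether women should go on being exposed to SWI. The second raises whether evidence of benefit is strong enough to act on early. The same holds for instrumental birth, where the protocol's own background points to a possible excess on SWI in particular.

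The stake reaches beyond the trial, because SWI is already available at three of the sites (Care during labour). Evidence against SWI would matter to women treated there outside the trial. Evidence against a saline placebo would not.

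**Working it through.** **1. Reproduce the planning figure.** Inputs from Sample size: 17.5% v 12.5%, power 80%, type I error 0.05, taken as two-sided in line with Statistical methods.

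- Without continuity correction: n = [1.96 × √(2 × 0.15 × 0.85) + 0.8416 × √(0.175 × 0.825 + 0.125 × 0.875)]² / 0.05² = 799.4, so 800 per group.
- With continuity correction: n′ = (n/4) × [1 + √(1 + 4/(n × 0.05))]² = 839 per group, which matches the protocol exactly.
- With 10% attrition: 839 / 0.90 = 932.2, so 933 per group and 1866 in total. This is the Abstract's total. The Sample size section gives 1886.

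**2. Place the interim look.** Half of 1866 is 933 women (466.5 per arm). Half of 1886 is 943 women (471.5 per arm).

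**3. What coded groups would show at the design rates, using 943 women.**

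- Expected caesareans: 0.175 × 471.5 = 82.5 in one group and 0.125 × 471.5 = 58.9 in the other.
- Standard error: √[(0.175 × 0.825 + 0.125 × 0.875) / 471.5] = 0.0232. Expected |z| = 0.05 / 0.0232 = 2.16.
- Chance of a nominal two-sided p < 0.05: Φ[(0.05 − 1.96 × √(2 × 0.15 × 0.85 / 471.5)) / 0.0232] = 0.576. After 10% attrition it is 0.532. With 933 women the two figures are 0.571 and 0.528.

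A conspicuous difference at this look is therefore more likely than not if the planning assumptions hold.

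**4. Swap the labels.** Suppose group A has 17.5% and group B 12.5%.

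- If A is saline, the relative risk on SWI is 12.5 / 17.5 = 0.71.
- If A is SWI, the relative risk on SWI is 17.5 / 12.5 = 1.40.
- The counts, |z| and power (0.576) are the same in both cases. Coded data give the size and leave the sign open.

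**5. The same for instrumental birth.** An odds ratio of 1.91 for A against B is 1.91 for SWI if A is SWI, and 1 / 1.91 = 0.52 if B is SWI. The committee could not say whether its own data agree with the earlier signal or run against it.

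**6. Set the tasks against what coded data allow.**

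- Check of sample size and power: feasible. It needs the size of the caesarean difference, and the test is two-sided.
- Safety and efficacy: an imbalance can be seen, but it cannot be attributed to SWI or to saline.

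**The case against.** The strongest reply is that the section can be carried out as written. Coded groups keep the committee blinded to allocation and still show it a difference between groups. That is right. A reader might infer that the two instructions are logically incompatible, but coded reporting satisfies both. Reading the plan as pooled reporting does not fit, because the same section asks for a between-group difference.

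A reader might also infer that the trial could be resized for the wrong reason. The documents do not support that either: the sample-size check does not depend on which label is SWI.

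A second reply is that review by coded arms, with codes opened on need, is a recognised arrangement, and that its mechanics usually sit in a charter that is not shown here. This has weight. It limits how firmly one can say that the committee will never learn the identities, and it shows that full unblinding from the outset is not required. It does not remove the point. The article does more than leave the matter open: it states blinding as the rule and names no exception, so a charter giving access would need that sentence to be qualified.

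A third reply is that the committee could presume that the arm with fewer caesareans is SWI. That assumes the hypothesis under test. Nor would a guess from pain scores be a sound basis for safety advice.

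**Conclusion.** The point holds in a limited form. Followed as written, the one described comparative look, at about 933 to 943 women, cannot attribute a difference in caesarean or instrumental birth to SWI as benefit or as harm. The loss is the whole of the sign: the same coded counts fit a relative risk of 0.71 or 1.40. The illustration assumes 1:1 allocation (implied by equal group sizes), the protocol's planning rates and reporting by coded arm.

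It would be tempting to turn the odds ratio of 1.91 into a number of extra instrumental births caused by the blinding. The documents do not support such a figure. They give no baseline rate, the confidence interval (0.95 to 3.84) includes 1, and nothing says that the committee would halt recruitment over a secondary outcome. The earlier result is a signal to watch, not an established harm.

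This should be corrected before the interim look. It does not invalidate the design or the final analysis. The remaining uncertainty is whether a charter already provides access to the codes.

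**What to change.** Replace the blanket statement that the DSMC is blinded with wording such as:

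*An independent statistician gives the DSMC closed-session results by arm, coded if preferred, with the arm identities available to DSMC members whenever they need them to judge safety or efficacy. Investigators, site staff, participants and the sponsor stay blinded.*

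If a charter already says this, align the protocol sentence with it. While editing, reconcile the totals of 1866 and 1886 so that the 50% trigger is a single number.

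The cost is one sentence and release of the randomisation list to an independent statistician. Sample size, outcomes and site procedures do not change. The small downside is that a few committee members may know the allocation. The protocol gives them no role in recruitment, care or outcome collection. The bias described under Randomisation and blinding, where the primary midwife could guess the arm from the woman's reaction, does not arise through them.

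### An efficacy look and an effect-based sample-size check at half enrolment sit beside an unreduced final P<0.05, so the stated 5% type I error is not guaranteed if either can change the trial

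*Protocol article*

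**What the plan says.** Three sections of the protocol article bear on this.

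- **Data safety and monitoring** plans one interim analysis: "The DSMC, which will be blinded to treatment allocation, will undertake interim analysis for safety and/or efficacy once 50% of the women have enrolled". It gives that analysis two tasks: to look for untoward outcomes, and to "ensure sample size and power calculations are appropriate based on the observed difference between groups for the primary outcome".
- **Statistical methods** sets one criterion throughout: "All study outcomes will be analysed using a two-sided P value of < 0.05 to indicate statistical significance". The primary outcome, caesarean section in labour, falls under it.
- **Sample size** states that "our study requires 839 women in each group (80% power, type I error 0.05", for a fall in the caesarean rate from 17.5% to 12.5%.

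The article gives no interim significance level, no reduced final level, no rule for changing the sample size, and no statement of whether the interim can stop the trial for efficacy. Interruption of the study lists examples of reasons for early termination. Efficacy is not among them, but the list is not exhaustive.

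**The concern.** A final test at 0.05 uses the full error allowance. If efficacy can also be declared at half enrolment, whatever is spent there comes on top, so the total exceeds 5%. An analysis plan could supply an interim boundary, but it could not bring the total back to 5% without departing from the final level that the article already states.

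The sample-size check raises a second, separate issue. If the final size depends on the interim treatment difference, the ordinary final test no longer has a guaranteed 5% error rate. Whether it is exceeded depends on the rule.

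At stake is the error rate of the primary comparison, the only one the article says the trial is powered for. It is easy to settle in advance and hard to repair credibly once half-trial results have been seen.

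**Working it through.** **Inputs.** From Sample size: rates 17.5% and 12.5%, type I error 0.05, power 80%, "839 women in each group". From Statistical methods: two-sided 0.05 at the end. From Data safety and monitoring: one look at 50% enrolment, taken as information fraction 0.5. The interim level and the re-sizing rule are not given, so they are assumptions and are shown as ranges. The enrolment total after attrition does not enter, because only the information fraction matters.

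**1. The plan's own figure.** Pooled rate (17.5% + 12.5%)/2 = 15.0%. For a two-sided 0.05 test with 80% power:

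n = [1.960·√(2·0.15·0.85) + 0.8416·√(0.175·0.825 + 0.125·0.875)]² / 0.05² = 799.4, so 800.

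With continuity correction: (799.4/4)·[1 + √(1 + 4/(799.4·0.05))]² = 838.9, so 839. This matches exactly. The design is a fixed-sample one with no allowance for an interim look.

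**2. Efficacy stop, final test left at 0.05.** Under the null hypothesis the interim and final statistics are bivariate normal with correlation √0.5 = 0.707. Overall error = 1 − P(|Z₁| < c₁ and |Z₂| < 1.960).

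| Assumed interim level (two-sided) | c₁ | Overall type I error |
|---|---|---|
| No stop and no size change | – | 5.00% |
| 0.001 | 3.291 | 5.02% |
| 0.0031 (Lan-DeMets, O'Brien-Fleming type) | 2.963 | 5.10% |
| 0.0052 (O'Brien-Fleming) | 2.797 | 5.20% |
| 0.05 (the only level the article states) | 1.960 | 8.31% |

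If outcome information at the look were 45% or 40% instead of 50%, the last row would be 8.5% or 8.6%.

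**3. Re-sizing on the observed difference, no efficacy stop, ordinary final test.** Assumed rule: with n₁ = 419.5 per group at the interim, the new size per group is N = n₁·[(1.960 + 0.8416)/|Z₁|]², which gives 80% power at the observed difference, capped at a multiple of 839. The final statistic is Z = [√n₁·Z₁ + √(N − n₁)·e]/√N, with e an independent standard normal, tested at |Z| > 1.960. Results from 4 million simulated null trials:

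| Cap (multiple of 839) | Size can only increase | Size can also decrease |
|---|---|---|
| 1.5 | 5.6% | about 6.5% |
| 2 | 6.0% | 6.8% |
| 3 | 6.4% | 7.2% |

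The 6.5% entry moves by about 0.1 point with the details assumed for the decrease. If the size is increased only when the interim trend is promising (|Z₁| > 1.960·√0.5 = 1.386), the error is about 4.8%, so there is no inflation.

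**4. Precision of the interim difference.** Its standard error at the planned rates is √[(0.175·0.825 + 0.125·0.875)/419.5] = 0.0246, about 2.5 percentage points against a planned difference of 5. It is a weak basis for resetting the size, apart from the error rate.

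**5. Levels that restore 5%.** Interim 0.001 with final 0.0498, or interim 0.0031 with final 0.0490, each gives 5.0% overall. Power of the final test at 839 per group (normal approximation, no continuity correction) is 81.87% at 0.05, 81.82% at 0.0498 and 81.64% at 0.0490.

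**The case against.** The strongest reply is that the article states no efficacy stopping rule. It mentions efficacy as a possible purpose, then describes the look in terms of untoward outcomes and of checking the sample size. A look that neither stops the trial nor changes its size leaves the error at 5%. Boundaries and committee procedures commonly sit in an analysis plan or charter, which are not shown, and their absence from a journal article is not a fault. All this stands, and it makes the point conditional. It does not remove it, because the article itself names efficacy, fixes the final level at 0.05 and fixes the basis of the size check.

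Three stronger readings are tempting, and the document does not support them.

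- *That the trial will have a false-positive rate well above 5%.* This needs both an efficacy stop and a lenient interim level. With a strict level the excess is 0.02 to 0.2 points. The 8.3% figure assumes 0.05 at the interim.
- *That an ordinary final test is always invalid after effect-based re-sizing.* It depends on the rule, as the promising-trend rule above shows.
- *That a committee blinded to allocation cannot do its safety work.* Comparing coded groups, with the codes opened if an imbalance appears, is an accepted arrangement, and the committee also reviews all adverse events. What remains is a minor gap in wording: the article does not say how a blinded committee sees the difference between groups.

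**Conclusion.** The point holds in conditional form and should be fixed. As written, an efficacy look and an effect-based size check stand beside a final level that leaves no error for either. The 5% in Sample size is therefore assured only if the interim can neither stop for efficacy nor change the size, or if any change follows a rule that happens not to inflate the error.

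For an efficacy stop the plausible range is 5.02% to 8.3%, governed entirely by the unstated interim level. For re-sizing alone it is 5.6% to 7.2% across the assumed rules that aim for 80% power at the observed difference, and there is no excess under a promising-trend rule. These figures assume information fraction 0.5 and normal approximations. The re-sizing figures also assume the caps shown. The conflict between the stated rules is certain; its numerical size is not.

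**What to change.** 1. **Data safety and monitoring, efficacy.** Either state that the interim analysis cannot stop the trial for efficacy, in which case the look itself leaves the final 0.05 intact, or set a strict interim level: P<0.001 with a final level of 0.0498, or about 0.003 with a final level of 0.049.
2. **Statistical methods.** If an efficacy stop is kept, give the matching final level for the primary outcome in place of 0.05.
3. **Data safety and monitoring, sample size.** Replace the check on the observed group difference with a blinded check of the pooled caesarean rate against the planned 15.0%. If effect-based re-sizing is really wanted, state the rule and use a final test that preserves the error rate.
4. **Minor.** Say how a committee blinded to allocation sees the group difference, for example by coded groups with a provision to open the codes.

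**Cost.** Protocol wording and a matching charter. At 839 per group, final-test power falls by 81.87 − 81.82 = 0.05 points or 81.87 − 81.64 = 0.23 points, depending on the pair chosen, so the planned size need not change. The drawback is that a pooled-rate check guards against a wrong event rate but not against a wrong effect size.
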